## **8.2 TReg Functional Assays**

The functional capacity of CD4+CD25+CD127 TRegs will be assessed, as described by us previously (Fecci, Mitchell et al. 2006), and comparisons will be made between groups that randomly received saline or daclizumab. Briefly, leukapheresis samples are diluted, underlayered with Ficoll (Histopaque 1077, Sigma), and spun for 25 mins. Interphases are collected, washed extensively, and subjected to a 2 hour adherence step to remove monocytes. A CD4+ T-Cell Isolation Kit II (Miltenyi) is used to isolate untouched CD4+ cells according to the manufacturer's instructions using a biotinylated antibody cocktail specific for non-CD4+ (CD8, CD14, CD16, CD19, CD36, CD56, CD123, TCR $\gamma\delta$  and Glycophorin A) and anti-biotin microbeads. CD127-biotin (BD, #558633) is also added to the isolation cocktail to deplete CD127+ cells. CD25+ cells are further isolated using Miltenyi CD25-beads (#130-090-445). Alternatively, unlabeled fractions (CD4+CD127) are labeled with a non-overlapping  $\alpha$ CD25-PE (MA251, BD Pharmingen (#555432)) and  $\alpha$ CD45RO-FITC (UCHL1) and sorted into CD25+CD45RO+ (TRegs) and CD25 populations on an ARIA flow cytometer. Purity of obtained populations is always  $>98\%$ . Either approach yields a population of CD4+CD25+CD127 T-cells which have been shown by us to function as TRegs. To verify suppressive capacity amongst TRegs (suppression assay),  $5 \times 10^4$  CD4+CD25 responders are plated alone or with varying proportions of autologous TRegs to a maximum ratio of 1:1 in complete T-cell media consisting of RPMI + 10% FCS, supplemented with HEPES buffer, sodium pyruvate, penicillin/streptomycin, L-glutamine,  $\beta$ -mercaptoethanol, and non-essential amino acids. After 72 hours of culture, levels of proliferation are assessed by  $^3\text{[H]}$ -thymidine incorporation (Amersham, Piscataway, New Jersey). Cells are cultured for an additional 16 hours and then harvested on a FilterMate cell harvester (Perkin Elmer, Boston, Massachusetts).  $^3\text{[H]}$  counts were performed using a Wallac 1450 Microbeta Trilux® Liquid Scintillation / Luminescence Counter (Perkin Elmer). Data are taken as means of triplicate wells. As a subordinate assay, to verify energy (proliferation assay) in the TReg population,  $1 \times 10^5$  TRegs or CD4+CD25 cells are plated alone in triplicate wells using phytohemagglutinin (PHA) (0.1, 1, 5, 10, 20  $\mu\text{g/well}$ ) as a stimulator and analyzed similarly.

### **8.2.1 Statistical Analysis**

Our primary endpoint analysis will consist of a comparison of proliferative T-cell response to PHA among treatment groups (+/- daclizumab) using a generalized linear model for normal data that accounts for correlation of measurement replication across PHA doses (0, 0.1, 1, 10  $\mu\text{g/well}$ ) within subjects. This analysis determines whether the difference in treatment groups relative to proliferative response remains constant over 4 PHA doses (i.e. curves remain parallel or not). A test of interaction with 3 degrees of freedom will be used. If the curves deviate significantly from parallelism, we will conclude that the effect of treatment varies as a function of PHA dose level. Within the

context of this model, statistical contrasts will be used to assess treatment differences at specific PHA dose levels. If the test for interaction is not statistically significant, one will conclude that the treatment effect is constant over PHA dose levels. A generalized linear model without an interaction will be used to assess whether the main effect for treatment is statistically significant (i.e. treatment differences are non-zero). In this analysis and others, if assumptions required for t-tests are not satisfied, a non-parametric Wilcoxon rank sum test will be conducted at each PHA level. Significance for this and other assays will be taken at the  $\alpha=0.05$  level unless otherwise indicated. A Bonferroni correction will be used to control for the multiple comparisons.

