### 2.2 Objectives

#### 2.2.1 Primary Objective

- To determine if daclizumab inhibits the functional and numeric recovery of TRegs after therapeutic TMZ-induced lymphopenia in

---

 TTP, time to progression

the context of vaccinating adult patients with newly-diagnosed high grade gliomas using CDX-110.

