### **8.1.1 Overview of Statistical Analysis**

Our laboratory and the HVTN Immunologic Monitoring Reference Laboratory, headed by [name] also at Duke University, has devoted considerable effort to co-developing and co-validating the immunologic assays outlined below for monitoring  $T_{Reg}$  function, antigen-specific responses in CD8+ or CD4+ T-cells, and NK cell functional activity in cancer patients. The reproducibility of these assays in our hands ensures that they can be reliably used for monitoring of changes after vaccination with and without daclizumab. Power calculations for this study are based on our primary endpoint which is functional suppressive capacity of CD4+CD25+CD127-  $T_{Regs}$ . For these calculations, we assumed that measurements made in each treatment group at a given phytohemagglutinin (PHA) level would be normally distributed with standard deviation of  $\sigma$ . Based on our experience with these assays within this patient population (Fecci, Mitchell et al. 2006), we estimate that with a sample size of 20 randomized patients we will have 80% power to detect a difference of 1.41  $\sigma$  at the 0.017 significance level (one-tailed). A 0.017 level of significance is used to adjust (Bonferroni correction) for the use of 3 non-zero PHA doses (0.1, 1, 10  $\mu$ g/well) in the proliferation assay. Thus, with only 20 patients, we will have sufficient power to detect treatment effects much more subtle than the ones observed in our pre-clinical studies (Fecci, Sweeney et al. 2006) and effects that we believe would be clinically significant. However, because the magnitude and variability of the effects of daclizumab on  $T_{Regs}$  remain unknown in humans, once human data become available from these studies, power analyses will be recalculated and patient numbers adjusted if needed. If daclizumab treatment does not significantly inhibit the functional recovery of  $T_{Regs}$  (primary endpoint), we would not be interested in the further development of this drug as

a vaccine adjuvant. Therefore, a one-sided hypothesis test is utilized. Power calculations are not provided for subsequent analyses as the number of patients in this trial will be determined by the primary endpoint, and the remainder of the analyses is exploratory and hypothesis generating only. With 10 patients in each arm, however, we will have 80% power to detect difference  $>1.325\sigma$  between groups for each assay at  $\alpha=0.05$ .

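### The designated primary analysis and its power calculation use the subordinate PHA proliferation assay, not the suppression assay that measures the stated primary endpoint

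*Protocol*

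**What the plan says.** The primary objective in 2.2.1 is stated as: "To determine if daclizumab inhibits the functional and numeric recovery of T Regs after therapeutic TMZ-induced lymphopenia in" the vaccination setting. Section 8.1.1 then fixes the endpoint: "Power calculations for this study are based on our primary endpoint which is functional suppressive capacity of" CD4+CD25+CD127- TRegs.

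Section 8.2 describes two assays on the isolated cells:

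- The first is introduced with "To verify suppressive capacity amongst T Regs (suppression assay" and plates CD4+CD25- responders by themselves or with graded proportions of autologous TRegs, up to 1:1.
- The second is introduced with "As a subordinate assay, to verify energy (proliferation assay) in the" TReg population (the printed word is apparently meant to be anergy). It plates TRegs or CD4+CD25- cells alone, "using phytohemagglutinin (PHA) (0.1, 1, 5, 10, 20" µg/well).

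Section 8.2.1 then sets the primary analysis: "Our primary endpoint analysis will consist of a comparison of proliferative T-cell response to PHA among treatment groups (+/- daclizumab". The model is a generalized linear model with PHA dose (0, 0.1, 1, 10 µg/well) as the within-subject factor and a 3-df test of treatment by dose.

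Section 8.1.1 sizes the trial on 20 randomized patients, 80% power, a difference of 1.41 SD and a one-tailed level of 0.017. The SD is defined at a given PHA level. The 0.017 is a Bonferroni correction for three non-zero PHA doses in the proliferation assay. The same section says that without significant inhibition of functional TReg recovery there would be no interest in developing daclizumab further as a vaccine adjuvant. On sample size it adds: "power analyses will be recalculated and patient numbers adjusted if needed".

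**The concern.** The endpoint is a property of TRegs acting on other cells. The designated primary analysis is of cells cultured on their own under graded mitogen. Cells plated alone cannot show whether TRegs suppress responders. A significant PHA result would therefore not establish that daclizumab impairs suppression, and a null result would not refute it.

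This matters because 8.1.1 attaches a stop-or-continue decision to the primary test. As written, that decision would follow from the assay that the protocol itself ranks second. A later analysis plan could not supply the right test without contradicting the protocol, which already fixes the model, the alpha and the power.

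Two gaps add to the difficulty. Section 8.2.1 does not say whether the TRegs or the CD25- cells supply the T-cell response. Section 8.1.1 commits to a one-sided test, but no favourable direction is given for the PHA response.

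**Working it through.** **1. Match endpoint, assay and model.**

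| Item | Where | What it refers to |
|---|---|---|
| Primary endpoint | 8.1.1 | TReg suppressive capacity |
| Assay measuring it | 8.2 | Suppression assay; design factor is the TReg:responder ratio |
| Assay with graded PHA | 8.2 | Proliferation assay; cells alone; labelled subordinate |
| Primary model | 8.2.1 | PHA dose as repeated factor; no ratio term, no percent suppression |
| Alpha 0.017 | 8.1.1 | 0.05/3, for three PHA doses in the proliferation assay |
| SD | 8.1.1 | Per PHA level; no numerical value |

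The endpoint points to the suppression assay. The model, alpha and SD all point to the other one.

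**2. Reproduce the stated power.** Inputs from 8.1.1: n = 10 per arm, difference 1.41 SD, one-sided alpha 0.017. For a two-sample t-test, df = 2 × 10 − 2 = 18 and the noncentrality is 1.41 × √(10/2) = 1.41 × 2.236 = 3.153. The critical value t(0.983; 18) is 2.295. Power = P(noncentral t > 2.295) = 0.797, and the difference detectable with 80% power is 1.414 SD. The stated figure reproduces, so there is no arithmetic error. The companion figure of 1.325 SD reproduces at two-sided 0.05 (power 0.800).

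**3. What the calculation becomes for the suppression readout.** The protocol gives neither the number of TReg:responder ratios nor the SD of the readout. The number tested, k, is therefore an assumption, and results are in SD units of the suppression readout. With one-sided alpha 0.05/k, 10 per arm and 80% power:

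| k ratios tested | One-sided alpha | Detectable difference |
|---|---|---|
| 1 | 0.05 | 1.16 SD (1.156) |
| 2 | 0.025 | 1.32 SD |
| 3 | 0.017 | 1.41 SD |

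The stated 1.41 carries over only if exactly three ratios are tested.

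**4. Dependence on evaluable samples.** Section 8.2 starts from leukapheresis material. A further leukapheresis after vaccination is required only of patients with a positive PEPvIII skin test (5.2.1, 5.2.3, 8); the other post-vaccination samples are blood draws (6.2.4). Ten post-treatment values per arm are therefore not assured. If, as an assumption, 6 per arm are evaluable for one ratio at one-sided 0.05, then df = 10, the critical value is 1.812 and the detectable difference is 1.54 SD.

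**The case against.** The strongest defence is that the proliferative response to PHA means responder proliferation in the co-culture, since both assays read thymidine uptake. This fails. Section 8.1.1 says proliferation assay, 8.2 gives that name to the subordinate assay, 8.2 describes no PHA series for the suppression assay, and the model has no ratio term.

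A second defence has some force. Section 8.2 promises, in general terms, a between-group comparison of TReg functional capacity. The PHA assay bears on one aspect of TReg function. TReg counts have their own t-test in 8.3.1. A reader might infer that suppression is never tested, or that power for it is zero. The documents do not support either. A comparison is promised but no test of it is fixed here, and an unspecified test has undefined power, not zero.

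Three other tempting readings also go too far:

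- **Dose lists.** Section 8.2 plates five non-zero doses while 8.1.1 and 8.2.1 agree on three. Analysing three of five plated doses is not in itself an error; the protocol only needs to say which are analysed.
- **Sample-size adjustment.** A type I error of 0.078–0.083 can be produced by simulation. It assumes a rule that tests at one-sided 0.05, extends to 20–40 per arm on the observed effect if the first result is positive but not significant, and retests at 0.05. The protocol contains no such rule, and it caps enrollment at 40 overall. The figure is illustrative only.
- **1.16 against 1.41 SD.** This is not a like-for-like gain. It compares one test with three, on readouts whose SDs are not given.

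It can also be said that post-treatment material may be short for a suppression assay. That is true, but the PHA assay uses the same isolated cells from the same samples and faces the same limit. It is a reason to state the evaluable number, not to keep the PHA analysis as primary.

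**Conclusion.** The point holds and should be corrected before the primary analysis is run. The designated primary analysis in 8.2.1 and the power calculation in 8.1.1 address PHA-driven proliferation of cells plated alone, not the suppressive capacity named as the primary endpoint. The go/no-go statement therefore rests on a test that does not measure what it is about. This conclusion comes from the protocol's own labels and needs no outside figure.

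In size, the stated 80% power at 1.41 SD is correct for the PHA readout at one-sided 0.017. It says nothing about suppression unless three ratios are tested and 10 patients per arm are evaluable. The restated differences depend on the assumed number of ratios and evaluable patients, on normality, and on an SD that the protocol does not give.

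**What to change.** - **8.2.1:** make the primary response a suppression-assay readout, for example percent suppression of CD4+CD25- responders at one prespecified TReg:responder ratio and one time point. Test it one-sided, with the direction stated as lower suppression with daclizumab.
- **8.1.1:** restate alpha and the detectable difference for that readout: about 1.16 SD at one-sided 0.05 with one ratio and 10 evaluable per arm, or 1.41 SD with Bonferroni over three ratios. State the number of patients expected to have a post-treatment sample, and the consequence of a shortfall (about 1.54 SD for one ratio with 6 per arm).
- **8.2 and 8.2.1:** move the PHA curve to secondary. State which cell population and which plated doses are analysed.
- **Side point, 8.1.1:** limit any re-sizing to the blinded pooled SD, or delete the sentence.

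The suppression assay is already described in 8.2, so the cost is mainly an amendment to protocol wording. The one practical check is whether enough post-treatment material will exist in both arms.

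### The primary model counts unstimulated wells (PHA 0) as a fourth dose level, which blurs the parallelism test and can dilute the pooled treatment effect, at a modest cost in power

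*Protocol*

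**What the plan says.** Section 8.2.1 (Statistical Analysis) describes the primary analysis as a "comparison of proliferative T-cell response to PHA among treatment groups". It uses a linear model for normal data that "accounts for correlation of measurement replication across PHA doses (0, 0.1, 1, 10" µg/well) within subjects. The parallelism question is put over all four levels: "This analysis determines whether the difference in treatment groups relative to proliferative response remains constant over 4 PHA doses". The degrees of freedom confirm that zero is a tested level: "A test of interaction with 3 degrees of freedom will be used".

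Both outcomes are fixed. If the curves are not parallel, "we will conclude that the effect of treatment varies as a function of PHA dose level", and contrasts at specific dose levels follow. If the test is not significant, "one will conclude that the treatment effect is constant over PHA dose levels", and one main effect is tested in the model without interaction. The significance level is 0.05 unless stated otherwise, with a Bonferroni correction for multiple comparisons.

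Section 8.1.1 (Overview of Statistical Analysis) computes power for a comparison at a given PHA level with a common standard deviation σ. It sets the one-sided level at 0.017 because of "the use of 3 non-zero PHA doses" (0.1, 1 and 10 µg/well).

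Section 8.2 (T-Reg Functional Assays) says that in the proliferation assay the cells "are plated alone in triplicate wells using phytohemagglutinin (PHA) (0.1, 1, 5, 10, 20" µg/well). That list adds 5 and 20 and does not mention wells without PHA.

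**The concern.** PHA is the stimulator. If treatment acts on the response to PHA, wells without PHA show little of that action. The four treatment differences are then close to (0, d, d, d) even when the effect is the same at every stimulated dose.

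Two consequences follow. First, the parallelism test partly asks whether daclizumab has any effect on stimulated cells, not whether the effect changes between 0.1, 1 and 10 µg/well. Its rejection is nevertheless to be reported as an effect that varies with PHA dose. Second, when the test does not reject, the single pooled effect includes a term near zero and understates the effect on stimulated response.

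Section 8.1.1 makes this endpoint decide whether daclizumab is developed further as a vaccine adjuvant, so both the description and the size of the effect matter.

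**Working it through.** **Inputs.** From 8.1.1: 20 randomised patients, 10 per arm, common σ, planning difference 1.41 σ, one-sided level 0.017. From 8.2.1: levels 0, 0.1, 1 and 10 µg/well, 3-df interaction, level 0.05. Assumed, because the protocol does not give them: no treatment effect at PHA 0, an equal effect d at the other three levels, exchangeable within-patient correlation ρ, and a standard deviation at PHA 0 equal to the others unless stated.

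**1. The plan's own figure.** 0.05/3 = 0.0167, rounded to 0.017. Two-sample t-test, 18 df, noncentrality 1.41 × √(10/2) = 3.15. Power is 79.7% one-sided, so the stated 80% reproduces.

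**2. Interaction test over four levels.** The mean of (0, d, d, d) is 0.75d. The squared deviations sum to 0.5625d² + 3 × 0.0625d² = 0.75d². The noncentrality of the repeated-measures F(3, 54) test is

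λ = (10/2) × 0.75d² / [σ²(1 − ρ)] = 3.75 (d/σ)² / (1 − ρ).

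At d = 1.41 σ and ρ = 0.5, λ = 3.75 × 1.988 / 0.5 = 14.9.

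Probability that the test rejects:

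| ρ | d = 1.41 σ | d = 1.0 σ |
|---|---|---|
| 0 | 58% | 32% |
| 0.3 | 76% | 44% |
| 0.5 | 89% | 59% |
| 0.7 | 99% | 83% |

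At ρ = 0.8 and 1.41 σ it is about 100%. The multivariate version, F(3, 16), gives 51 / 68 / 83 / 97% at 1.41 σ for the four values of ρ in the table. With the three non-zero doses only, the differences are (d, d, d) and the 2-df test rejects at its nominal 5%.

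**3. Main effect when the interaction is not significant.** With equal weights the estimate is (0 + d + d + d)/4 = 0.75d. For d = 1.41 σ that is 1.06 σ, or 25% too small. In simulation with a common σ, the mean estimate among trials with a non-significant interaction is 0.75d to 0.78d. If PHA 0 wells vary less than the others and the model weights by variance, the dilution is larger. With half the standard deviation at PHA 0, the estimate is 0.43d at ρ = 0 and 0.21d at ρ = 0.3.

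**4. Power of the main-effect test on its own.** The variance of a patient's mean over k levels is σ²[1 + (k − 1)ρ]/k. At ρ = 0.5 the noncentrality is 1.06/√(0.2 × 0.625) = 2.99 with four levels, and 1.41/√(0.2 × 0.667) = 3.86 with three. Two-sided 5% power is 81% against 95%.

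**5. Power of the whole planned sequence.** Step 4 is not the operative power, because a significant interaction sends the analysis to dose-specific contrasts. The full sequence was simulated: interaction at 0.05; if significant, Bonferroni contrasts at the three non-zero doses, success if any is significant; otherwise the main effect. Settings were ρ = 0.3-0.8 and a standard deviation at PHA 0 of 0.1 or 1 times the others. At 1.41 σ, one-sided power is 90-99% as written and 95-99% with three doses, a loss of about 0-5 points. At 1.0 σ the loss is about 1-10 points one-sided, and up to about 11 two-sided.

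**The case against.** The strongest reply has four parts.

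*Absence of effect at PHA 0 is not in the protocol.* This stands. Section 3.12 reports that the mouse anti-CD25 antibody, given without vaccine to temozolomide-treated mice, increased overall T-cell expansion, so a shift in unstimulated wells is conceivable. An equal shift at all four levels would remove the problem. The argument is therefore conditional.

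*The interaction conclusion is not false.* If there is no effect at zero and an effect d elsewhere, the effect does vary with PHA level. This stands as far as it goes. What the result cannot support is a statement about dose dependence among the stimulated doses, which is how a reader would take it.

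*The powered contrasts are intact.* This stands. After a significant interaction, the contrasts at 0.1, 1 and 10 µg/well are unbiased and are the comparisons that 8.1.1 powers. At the design effect most trials take that branch. A reader might take the drop from 95% to 81% in step 4 as the power lost by the primary analysis; it is not, because that test is used only when the interaction is not significant.

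*The dose lists conflict less than they seem to.* A reader might infer three incompatible dose sets. Sections 8.1.1 and 8.2.1 agree on 0.1, 1 and 10, and the word non-zero in 8.1.1 implies a zero level. The list in 8.2 gives stimulating doses for a subordinate assay and need not name unstimulated wells. What remains is that 5 and 20 µg/well are plated but not modelled, and that 8.2 does not say PHA 0 is plated. A reader might also infer that every other assay subtracts background. Several do (8.5.1, 8.6.1, 8.8.1, 8.9.1, 8.12.1), but section 8.4 cultures cells at 0, 5 and 10 µg of PHA and its analysis section, 8.4.1, states no subtraction.

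**Conclusion.** The point holds in a limited form. Section 8.2.1 makes PHA 0 a tested level in both the interaction and the main effect, which fits neither its named target nor the power basis in 8.1.1. If daclizumab has little or no effect in unstimulated wells, a constant effect of 1.41 σ over the stimulated doses triggers the interaction in about 76-100% of trials for ρ of 0.3-0.8. The rejection then says nothing about dependence among those doses. In the remaining trials the pooled effect is about 25% too small under equal weights.

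For effects well below 1 σ, the interaction is no longer usually significant unless ρ is high. The documents do not support the stronger reading that the primary endpoint is underpowered or its decision invalid: over the whole sequence, power at 1.41 σ stays above the planned 80%. The main harm is to interpretation and effect size, with a modest loss of power.

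**What to change.** In 8.2.1, fit the treatment-by-dose interaction (2 df) and the main effect to 0.1, 1 and 10 µg/well only. Use the PHA 0 value as background, either subtracted from each stimulated value or entered as a covariate. In 8.2, state that PHA 0 wells are plated and that 5 and 20 µg/well are not part of the primary analysis.

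This is a wording change and needs no data beyond the PHA 0 wells that 8.2.1 already assumes. The downside is small: subtracting a noisy background can add variance, and the covariate form avoids that.

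### The primary analysis in 8.2.1 (non-directional interaction gate, then possibly a single main-effect test over four PHA doses) is not the one-sided 0.017 per-dose test that 8.1.1 powers

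*Protocol*

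**What the plan says.** Protocol 8.1.1 bases the power on the primary endpoint. It states that "with a sample size of 20 randomized patients" there is "80% power to detect a difference of 1.41" SD, "at the 0.017 significance level (one-tailed"). The 0.017 is a Bonferroni adjustment for three non-zero PHA doses (0.1, 1 and 10 µg/well). The protocol adds that daclizumab would not be developed further as a vaccine adjuvant unless it significantly inhibits TReg recovery: "Therefore, a one-sided hypothesis test is utilized". For the remaining, exploratory assays it gives 80% power for 1.325 SD at 0.05 ("With 10 patients in each arm, however").

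Protocol 8.2.1, which sets out the primary endpoint analysis, describes a different sequence:

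- A repeated-measures model over four doses: 0, 0.1, 1 and 10 µg/well.
- "A test of interaction with 3 degrees of freedom will be used".
- If the curves are not parallel, contrasts at specific doses within that model.
- If the interaction is not significant, a model without it, to assess "whether the main effect for treatment is statistically significant (i.e. treatment differences are non-zero").
- "Significance for this and other assays will be taken at the" 0.05 level except where the protocol indicates another, with a Bonferroni correction over an unstated number of comparisons.

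**The concern.** The two sections differ in dose set (three against four), structure (parallel per-dose tests against a gated sequence) and, on one branch, direction and level. The interaction test has no direction. The main-effect branch is a single test, so the three-dose Bonferroni argument for 0.017 does not apply to it, and its alternative is described as non-zero. It also averages in the 0 dose, which 8.1.1 leaves out.

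This is the one test to which the protocol ties a development decision; 8.1.1 calls the other analyses exploratory. If the powered test and the described test differ, the stated power does not apply to the analysis that will be run. The protocol also does not say which result settles the question.

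**Working it through.** **Inputs from the protocol.** 20 randomised, 10 per arm, so 18 df; 1.41 SD; 80% power; one-sided 0.017 (0.05/3 = 0.0167); 1.325 SD at 0.05; the four doses and 3-df test of 8.2.1.

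**Step 1: reproduce the stated figures.** Power = P(T > t_crit), with T noncentral t on 18 df and noncentrality δ√(n/2). For δ = 1.41 and n = 10 this is 1.41 × √5 = 3.15.

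| Test | t_crit | Power at 1.41 SD | Difference at 80% power |
|---|---|---|---|
| one-sided 0.017 | 2.295 | 0.797 | 1.414 SD |
| two-sided 0.017 | 2.630 | 0.697 | 1.570 SD |
| one-sided 0.05 | 1.734 | 0.917 | 1.156 SD |
| two-sided 0.05 | 2.101 | 0.846 | 1.325 SD |

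The 1.41 SD figure is the one-sided 0.017 single-dose t-test. The 1.325 SD figure is the two-sided 0.05 t-test. Both are correct for those tests.

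**Step 2: what the main effect tests.** With four equally correlated doses, the per-patient mean has variance σ²(1 + 3ρ)/4. Its SD is √0.40 = 0.63σ at ρ = 0.2 and √0.85 = 0.92σ at ρ = 0.8. An effect of 1.41σ at one dose becomes 1.41/4 = 0.35σ in the mean, which is 0.35/0.63 = 0.56 or 0.35/0.92 = 0.38 standardised units. An effect of 1.41σ at every dose stays 1.41σ and gains from the smaller SD. The main effect is therefore a different statistic from the one powered, weaker or stronger according to the pattern.

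**Step 3: simulate both rules.** There were 40,000 runs per case, with normal data, equal correlation across doses (assumed; the protocol gives none) and the interaction tested at 0.05. The 8.1.1 rule is any of three doses at one-sided 0.017. The 8.2.1 path was read three ways:

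- (a) one-sided contrasts at 0.05/3, main effect one-sided 0.017;
- (b) the same contrasts, main effect one-sided 0.05;
- (c) two-sided contrasts at 0.05/3, main effect two-sided 0.05, counting only favourable rejections.

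| Effect | ρ | 8.1.1 | 8.2.1 (a) | (b) | (c) |
|---|---|---|---|---|---|
| 1.41 SD, one non-zero dose | 0.2 | 0.804 | 0.689 | 0.738 | 0.649 |
| | 0.5 | 0.796 | 0.760 | 0.773 | 0.676 |
| | 0.8 | 0.799 | 0.796 | 0.796 | 0.696 |
| 1.41 SD, all four doses | 0.2 | 0.981 | 0.995 | 0.999 | 0.996 |
| | 0.5 | 0.953 | 0.948 | 0.985 | 0.964 |
| | 0.8 | 0.900 | 0.863 | 0.949 | 0.896 |
| 1.0 SD, all four doses | 0.2 | 0.823 | 0.885 | 0.960 | 0.916 |
| | 0.5 | 0.751 | 0.711 | 0.859 | 0.765 |
| | 0.8 | 0.654 | 0.571 | 0.753 | 0.633 |

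When the effect is equal at all doses, the interaction is significant in about 5% of trials, so the powered contrasts are seldom reached. Under (c), the 8.1.1 and 8.2.1 verdicts differ in about 8 to 16% of trials for the single-dose 1.41 SD and all-dose 1.0 SD patterns.

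**The case against.** The strongest reply is that the protocol, read as a whole, already settles most of this. 8.1.1 says the primary test is one-sided, and its criterion (significant inhibition) is directional. The 0.05 level in 8.2.1 yields wherever another level is given, and 8.1.1 gives 0.017. Several other assay sections say two-sided explicitly, while 8.2.1 does not, so the non-zero wording may be only a loose gloss. The contrasts sentence carries no condition of its own, so the gate is partly inferred.

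Much of this stands. The contrasts can fairly be read as one-sided 0.017, and the sample-size arithmetic is sound. The reply does not reach the other branch. A single main-effect test has no three-dose multiplicity to import, it uses a dose that 8.1.1 excludes, and it follows a test that has no direction. An SAP could supply detail, but it could follow only one of the two descriptions.

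Two stronger readings are tempting and should not be drawn. A reader might infer that one and the same observed difference is a go under one section and a no-go under the other, by applying the four critical values in Step 1 to it. Those are thresholds for a single-dose t statistic, whereas the 8.2.1 main effect is an average over four correlated doses, so that comparison does not set the two procedures against each other. A reader might also infer that a significant difference in the wrong direction would count as success. The requirement of inhibition in 8.1.1 rules that out.

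**Conclusion.** The mismatch is real but limited. The stated 80% power at 1.41 SD belongs to a one-sided 0.017 test at a single dose and does not describe the 8.2.1 procedure. What cannot be reconciled is the interaction gate and the main-effect branch, whose direction and level are unsettled and which includes the 0 dose.

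For 1.41 SD at one dose only, power under 8.2.1 runs from about 0.65 to just under 0.80, against 0.80, depending on correlation, sidedness and level. With one-sided tests the loss all but disappears at correlation 0.8. For 1.41 SD at all doses both rules have about 0.86 or more, so the plan is not underpowered in general. All simulated figures rest on an assumed correlation of 0.2 to 0.8, equal across doses, on normal data and on the levels listed above.

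**What to change.** In 8.2.1, make the decisive primary test the one that was powered: one-sided contrasts at 0.1, 1 and 10 µg/well in the direction of reduced TReg function, each at 0.0167 (or Holm at one-sided family-wise 0.05), within the repeated-measures model already named. State what that direction means for the measured proliferation. Report the interaction and main-effect tests as supportive, not as a gate.

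This takes a few sentences, with no new data and no change in sample size. The small downside is some loss of power when the effect is equal at all doses and correlation is low: for 1.0 SD at correlation 0.2, 0.82 against 0.885 to 0.96. Against a main effect at one-sided 0.05, some loss remains at higher correlation too (0.65 against 0.75 at 0.8).

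If the sponsor prefers to keep the gated path, 8.2.1 should state the main effect as one-sided with its alpha and leave the 0 dose out of it. 8.1.1 should then restate the power for that procedure, with the correlation assumed.
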